### Pain management

Special care different from the patient’s own reality will not be applied during the course of the trial; that is intended to resemble the real clinical applicability of the treatment as much as possible. In those patients who take opioid and non-opioid analgesics and/or neuromodulators as usual, medication will be documented in the baseline and follow-up controls. Likewise, if a patient undergoes any infiltration or surgical intervention in the same area affected by the trial intervention, this patient should be excluded from the clinical trial algorithm, and their data may not be used in the results from the date of surgery or infiltration {11d}.

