### Data collection {18a} {18b} {19} {27}

At baseline, patient demographics and prior failed therapies will be documented, including frequency, duration, type, and compliance, as well as magnetic resonance imagining (MRI) and electromyography (EMG) diagnostic tests. Documentation of analgesic use for the treatment of LLR will include frequency, dosage, and duration. All baseline and post-procedural follow-up points will include reported outcomes documented through completing the NPRS, ODS, MOAS, SF-12, and DN4 questionnaires and documentation of narcotic and non-narcotic analgesic medication usage. Device and procedure-related adverse events and all serious adverse events will be documented throughout the study period (Table 3).

The data collected will be stored in locked cabinets, and only the main researcher will have access to this information. Data will be recruited in a computer spreadsheet with password protection to ensure confidentiality. To ensure no error, the spreadsheet will be monthly monitored and audited by a researcher who is blind to the participants’ group allocation and has no conflict of interest.

All patients who leave the study for any reason will no longer have their data collected.

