### Monitoring, safety, and quality control

The primary safety endpoint is the incidence of device- and/or procedure-related adverse events, which will be compared statistically between the randomized groups using proportions of patients experiencing such an event. The endpoint will be met if this event rate is not significantly greater with ACS than with PhS. All study-related adverse events will be monitored and reported, including seriousness, severity, treatment, and relationship to the study device/procedure. Adverse events collected in this study will be determined by the mine investigator to be specifically related to the products or procedures used in the 2 treatment groups or one that is determined to be a serious adverse event {22}.

To date, all published studies with ACS have shown high safety rates and no side effects for what ACS product itself represents. Even so, any intervention can lead to an adverse effect, so their monitoring will be an essential condition in this protocol {11b}.

Once the study has started, given that the inclusion of patients will be progressive over time as they are recruited, just in case there is a worsening of pain of more than 25% in more than 50% of the patients, the study would be reconsidered and the recruitment would be stopped to analyze the data and check if the worsening is in patients whom the ACS therapy was applied. If this were the case, the study would be definitively stopped and a report would be given to the laboratory. The author responsible for the study will carry out this audit if necessary. The main investigator together with the rest of the authors will make the decision to terminate the trial early {17b} {21a}.

Any other adverse effect as far as the interventions are concerned will be collected and analyzed (if necessary, the second intervention would be canceled, and the patient would be withdrawn from the study) {11b} {21b}.

The main investigator is the only person who will be in charge of follow-up with clinical interviews at 30 days, 3 months, 6 months, and 12 months. A schedule of visits will be established for each patient for their greater adherence to the study and not to delay follow-up. Apart from the following-up visit controls, the patients will provide from a telephone number of pain unit for any doubts, changing pain characteristics, or new interventions they will receive. In that way, it provides an improving of adherence to protocol of the study {11c}.

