### Statistical analysis {20a} {20b} {20c} {18b}

A descriptive analysis will be carried out for all the data collected. The normality of the data will be studied using the Kolmogorov–Smirnov and Shapiro–Wilk tests. For continuous quantitative variables, descriptions of central tendency and dispersion will be presented: mean and standard deviation respectively in case the variables follow a normal distribution or median and interquartile range for those variables that are not normally distributed. For categorical (qualitative) variables, frequencies and percentages will be presented. The main outcome (improvement > 2 points) will be tested using a generalized linear mixed model (GLMM). The GLMM model fit will include a between-subject factor and will also include a random effect for the time (baseline, 1st month, 3th month, 6th month, and 12th month) and the interaction between group and time variables. The inclusion of the interaction terms allows for a formal test between the groups over time. For the other variables, the mean effects of the interventions and the differences between groups and their respective 95% confidence intervals will be calculated using regression linear mixed models for repeated measures, which will incorporate terms for the treatment groups, time, and interaction terms. Treatment coefficients versus time interactions will be equivalent to the estimates of the differences between groups. All models will be adjusted for chance imbalances in outcome between groups at baseline. There will also be analyses of the covariates collected, including age, gender, and duration of symptoms. The analyses will follow the principles of intention to treat, and no interim analyses will be performed. No additional analysis will be performed. If a patient drops out of treatment, no additional outcome will be collected. The significance level will be set at 5%, and SPSS for Windows will be used for the statistical analysis.

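### Outcomes after a same-area procedure, dropping out of treatment or withdrawal are barred or not collected, which contradicts the stated intention-to-treat analysis and loses 12-month data for reasons plausibly linked to pain

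*Protocol article*

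**What the plan says.** The protocol article, under Statistical analysis, sets the principle: "The analyses will follow the principles of intention to treat". Four rules elsewhere limit which outcomes exist or may be used.

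- **Same-area infiltration or surgery** (Pain management): "this patient should be excluded from the clinical trial algorithm, and their data may not be used in the results". The bar takes effect on the day of that procedure and does not reach back to earlier visits.
- **Dropping out of treatment** (Statistical analysis): "If a patient drops out of treatment, no additional outcome will be collected".
- **Leaving the study** (Data collection): "All patients who leave the study for any reason will no longer have their data collected".
- **Adverse effect** (Monitoring, safety, and quality control): where judged necessary, "the second intervention would be canceled, and the patient would be withdrawn from the study". The leaving-the-study rule then applies to that patient.

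The primary efficacy measure is NPRS response from baseline to 12 months (Abstract, Methods). It is analysed with a generalized linear mixed model (GLMM) over baseline and months 1, 3, 6 and 12. The missing-data paragraph of Statistical analysis compares attrition between arms. It then examines missing values among patients who completed follow-up, with complete-case or multiple-imputation sensitivity analyses under missing at random (MAR).

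**The concern.** Under intention to treat, a randomised patient who is willing to be followed keeps contributing outcomes after stopping treatment or receiving another procedure. Here such a patient has no usable 12-month outcome. The reason for the loss is plausibly the outcome itself: in persistent radicular pain, a further infiltration or operation at the treated site most likely reflects pain that did not resolve. That is an inference, but a reasonable one.

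The article describes MAR as missingness that does not depend on the unobserved outcome, and that is doubtful for these patients. If failures leave the 12-month data, the response rate among those remaining is too high in each arm, and the comparison depends on how removal differs between arms. A later analysis plan cannot restore outcomes that were never collected.

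**Working it through.** **1. The passages side by side**

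| Event | What is kept | What is lost | Covered by the missing-data check? |
|---|---|---|---|
| Same-area procedure | Visits before its date | All visits from its date | No, not a completer |
| Dropping out of treatment | Baseline | All later outcomes | No |
| Leaving, or withdrawn after an adverse effect | Visits before leaving | All visits after leaving | No |

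Treatment is two procedures 14 days apart, and the first post-baseline NPRS falls 30 days after the second (Trial intervention and blinding; Outcome measures and follow-up). A patient who drops out between the two procedures therefore has no post-baseline NPRS. No rule counts any of these patients as non-responders.

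**2. Inputs for an illustration**

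- From Sample size: expected response 65% (ACS) and 35% (placebo), 35 patients per arm.
- Not in the documents, so assumed: the share of each arm removed, *d*, and that every removed patient would be a 12-month non-responder.

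Observed rate among those remaining = *r* / (1 − *d*), where *r* is the true rate. With *d* = 0 this returns the plan's own figure: 65% − 35% = 30 points. This is a complete-case month-12 proportion, not the planned GLMM, which would recover part of the loss from earlier visits.

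**3. Same share *f* of failures removed in both arms**

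Here *d* = *f*(1 − *r*).

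| *f* | ACS | Placebo | Difference |
|---|---|---|---|
| 20% | 0.65/0.930 = 69.9% | 0.35/0.870 = 40.2% | +29.7 |
| 30% | 0.65/0.895 = 72.6% | 0.35/0.805 = 43.5% | +29.1 |
| 40% | 0.65/0.860 = 75.6% | 0.35/0.740 = 47.3% | +28.3 |

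Both rates rise clearly. The difference shrinks by 0.3 to 1.7 points.

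**4. Different share of failures removed by arm**

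- 10% of ACS failures and 30% of placebo failures: 0.65/0.965 − 0.35/0.805 = 67.4% − 43.5% = +23.9.
- The reverse: 0.65/0.895 − 0.35/0.935 = 72.6% − 37.4% = +35.2.
- No true effect (35% in both arms), with 10% of the ACS arm and 25% of the placebo arm removed: 0.35/0.90 − 0.35/0.75 = 38.9% − 46.7% = −7.8. With 35 per arm this is 3.5 against 8.75 patients, a gap of about five.

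**The case against.** Several points on the other side stand.

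- **Not all data are discarded.** A reader might infer from the exclusion wording that a re-treated patient vanishes from the primary analysis. The same sentence bars data only from the date of the procedure. Someone re-treated at month 8 still contributes months 1, 3 and 6, and where those visits already show non-response the GLMM uses that.
- **The treatment effect need not be overstated.** A reader might infer that dropping failures inflates the difference. With equal re-treatment per failure it shrinks slightly. Equal removal of 15% per arm would give 76.5% − 41.2% = +35.3, but that requires re-treating 15/35 = 43% of ACS failures and only 15/65 = 23% of placebo failures.
- **The null scenario needs an added cause.** In a blinded trial, equal response suggests equal expected re-treatment. The −7.8 points require chance or some reason other than pain response. The only loss figure in the article is 10% to follow-up (Sample size), well below the assumed 25%.
- **The routes differ.** Ending collection when consent is withdrawn does not breach intention to treat. Withdrawal after an adverse effect is conditional, and dropping out of treatment is confined to a 14-day window.
- **Safety follow-up is not clearly abandoned.** A reader might infer that it stops on withdrawal. Data collection also promises to document device- and procedure-related and serious adverse events over the whole study, and the monitoring section says other adverse effects will be collected and analysed. The passages are in tension; they do not show that safety data cease.
- **Attrition by arm will be compared.** That could reveal unequal loss, but it does not correct it.

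None of this removes the conflict between the stated principle and rules that deny a willing patient a 12-month outcome.

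**Conclusion.** The contradiction is in the text and should be resolved. It is plainest for same-area procedures and for dropping out of treatment. It also reaches patients withdrawn after an adverse effect, through the blanket rule on leaving. What is lost is every visit after the event, including the primary 12-month one, under circumstances that make MAR doubtful and outside the planned missing-data check.

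The size is unknown because no re-intervention rate is given. On the complete-case illustration, both response rates are inflated. The 30-point difference becomes about 28 to 30 points if failures are re-treated equally often in both arms, and shifts by more, in either direction, if they are not. These figures assume that all removed patients are failures and ignore what the GLMM recovers. The documents support no claim about the direction of bias.

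**What to change.** 1. Reconcile Pain management, Data collection, Monitoring and Statistical analysis with intention to treat. Delete the rule barring data after a same-area procedure and the rule ending outcome collection after dropping out of treatment.
2. Keep every randomised patient in the scheduled assessments unless consent is withdrawn, including those whose second injection is cancelled. This concerns follow-up only and changes no treatment decision.
3. Record the date and type of any same-area procedure. The pain-unit telephone line already invites patients to report new interventions.
4. Prespecify one handling for the primary responder analysis: either non-response after a same-area procedure, or observed NPRS regardless of it. Use the other as a sensitivity analysis. This is a choice of estimand and both are defensible; the second sits closer to the article's aim of reflecting ordinary practice.
5. Extend the missing-data sensitivity analyses to non-completers.
6. Reconcile the rule ending data collection on leaving with the promise to document adverse events over the whole study.

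**Cost:** a protocol amendment and a few extra questionnaires. Response rates may look lower, and under the non-response option a procedure done for an unrelated reason counts as failure. Recruitment began in February 2022, so outcomes of patients already removed may not be recoverable; their number should be reported by arm.

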## Discussion

This study intends to adopt a rigorously designed and implemented randomized controlled method to evaluate the efficacy and safety of the administration of PRF therapy, combined with ACS, on the DRG to reduce neuropathic pain in patients with persistent LRP. The aim of this study is to explore a treatment with greater efficacy and fewer side effects for patients with persistent LLR, who have found pharmacologic therapy, corticoid injection therapy, or surgery ineffective. This treatment, if proven effective, may then be used as a complementary treatment to a more persistent pain.

A number of clinical studies show that ACS (Orthokine®) therapy reduces pain and improves function, mobility, and health-related quality of life. Patients can be treated safely and effectively, and no other injection therapy (corticosteroids, hyaluronic acid, PRP) rivals its long-term efficacy in osteoarthritis or musculoskeletal pathologies [31–37]. The use of ACS (Orthokine®) therapy may help to reduce the number of surgeries, the dosage and frequency of pain killing medications, and therefore medical costs in the medium and long term.

To date, only the randomized clinical trial by Becker et al. has shown superiority of ACS over corticosteroids in lumbar radicular pain (3 epidural injections) [32]. Godek et al. in 2016 also proposed a pilot study in which he observed pain improvement in 15 patients who were injected with ACS under ultrasound vision in the foramen affected by lumbar disc herniation [50]. Kumar et al. proposed 20 patients with unilateral lumbar radiculalgia in whom he applied between 1 and 3 injections of ACS in the epidural space; the patients improved their pain at 3 weeks, 3 months, and 6 months, but there was no control group in any of two studies [51].

In all cases, there were no undesirable or secondary effects due to ACS that made the studies reconsider in terms of safety. There is even a randomized pilot study also by Goni in which ACS injections were at cervical epidural level and in which pain improvement was obtained compared to methylprednisolone [52].

The data, daily regular use, and yearlong experience suggest ACS (Orthokine®) serum is an effective and well-tolerated alternative to other injection therapies.

As Kuffler explains [53], the trigger axon regeneration and Schwann cell proliferation may assist in reducing neuropathic pain. All molecules contained in ACS could give that trigger point. This study aims to highlight the importance of neuromodulation at the molecular level and how treatment with ACS (rich in cytokines, growth factors and especially interleukins) can give a very advantageous synergy to treatment LLR compared to using only corticosteroids or even other platelet-rich plasma serum.

## Conclusions

If the hypothesis proposed in the study is proven, a great advance will be made in the treatment of LLR and even further neuropathic pain. If there is an improvement in pain in these patients and this has repercussions on an improvement in their quality of life and functionality, we will not only be contributing to the clinical improvement of pain itself but also contributing to the emotional and psychological part of life of these patients, transforming pain into a minimal symptom for it to cease to be a disease.

Furthermore, as future therapies, it will give rise to a new gateway to future applications of the ACS as a molecular therapy on other types of neuropathic pain such as trigeminal neuropathy, peripheral neuropathy, and syndrome of the complex regional pain, among others.

### Trial status

The protocol version number: 2, 1 September 2021.

Date recruitment began: 1 February 2022.

Approximate date when recruitment will be completed: 1 February 2024.

## Data Availability

Only the main investigator will have access to the final trial dataset, who signed a data confidentiality commitment letter {29}. In addition, the main investigator signed a commitment letter as well as a data confidentiality commitment letter performing functions as a clinical record reviewer {27}.

## Abbreviations

PRF: Pulsed radiofrequency
DRG: Dorsal root ganglion
ACS: Autologous conditioned serum
PhS: Physiological saline 0.9%
LLR: Lower limb radiculalgia
MIC: Minimal important change
NPRS: Numeric Pain Rating Scale
ODS: Oswestry Disability Scale
IASP: International Association for the Study of Pain
DUH: Dexeus University Hospital
IC: Informed consent
VAS: Visual analog scale
MOAS: Scale for Mood Assessment
MRS: Mood Rating Scale
EVEA: *Escala de Valoración del Estado de Ánimo*
SF-12: Quality of Life Test
DN4: Douleur Neuropathique 4 questions
MRI: Magnetic resonance imaging
EMG: Electromyography
